### Baseline assessment including OA classification

Demographic data for age, sex, profession, hand dominance, and medical history including previous surgeries to the hand are collected at the baseline assessment. All participants have a radiograph (posterior-anterior and lateral view) of the affected finger before inclusion. Radiographs taken within 6 months of inclusion are eligible. OA is classified according to the Kellgren–Lawrence classification, which grades OA based on osteophyte formation, narrowing of joint space, and sclerosis of the subchondral bone [17]. Grade 0 represents a normal radiograph, whereas 5 depicts a joint with large osteophytes, a severe narrowing of joint space, marked sclerosis, and certain bony deformity.

### Interventions

#### Treatment arm 1: PIP denervation

Surgical PIP-denervation is performed under local anesthesia (blood-less field with finger-ring or wide-awake local anesthesia no tourniquet (WALANT) according to the surgeon’s preference). A volar approach to the PIP joint is used and a 360-degree denervation is performed as described by Jiménez et al. [9]. The skin is closed by resorbable or non-resorbable sutures depending on the surgeons’ preferences. A soft dressing is applied and removed by the participant after 5–7 days. At 2 weeks postoperatively, a nurse removes non-resorbable sutures and examines the wound for signs of infection or stiffness. Unlimited active motion of the operated joint is encouraged immediately after surgery as tolerated by the participant. No formal hand therapy protocol is used, and participants do not receive any specific conservative treatment (orthoses, education, exercise) after surgery. However, if the finger is considerably stiff or swollen at suture removal, the participant is referred to the hand rehabilitation unit to get standard treatment for postoperative finger stiffness. The need for additional rehabilitation sessions is documented in the study notes.

#### Treatment arm 2: Patient education and exercise program

The education and exercise program follows a clinical routine practice protocol developed by the Department of Hand Surgery at Södersjukhuset in Stockholm. This specific protocol has not been evaluated in a clinical trial, but both the education and exercises are very similar to a previously published protocol in hand OA [19].

#### Education program

At study start, participants receive one 30-min face-to-face session containing oral and written information about the disease, its course and symptoms, treatment options, and self-management principles including joint protection. The information booklet (in Swedish) with general information and exercises is available as Additional file 2.

#### Exercise

The exercise program consists of four face-to-face or video sessions and one optional session (see below). Between sessions, participants are instructed to perform four motion-promoting exercises (Fig. 3) and four strength-promoting exercises (Fig. 4) at home three times a week with 10 repetitions for each exercise.

**Fig. 3 Fig3:**
[figure not shown]
Motion-promoting exercises

**Fig. 4 Fig4:**
[figure not shown]
Strength-promoting exercises

The unloaded active motion exercises (Fig. 3) promote isolated flexion/extension of PIP (Fig. 3c), global flexion/extension of the finger (Fig. 3a, b), and opposition to thumb (Fig. 3d). The participant is encouraged to hold for 3–5 s at end position.At study start: one face-to-face rehab session + information booklet including exercises to improve function and strength and reduce pain2–4 weeks after study start: one 30-min rehab session, face-to-face or video (follow-up, modification of exercises if the participant is unable to perform all exercises due to pain or other problems)3 months after study start: one 30-min rehab session, face-to-face (follow-up, modification of exercises if needed)4–5 months after study start: one optional rehab session if needed, face-to-face or video (follow-up, modification of exercises if needed)6 months after study start: one 30-min rehab session, face-to-face (follow-up, modification of exercises if needed)

### Concomitant care

Participants may use paracetamol or non-steroid anti-inflammatory drugs (NSAID) as needed during follow-up. Systemic or intra-articular glucocorticoids or intraarticular platelet-rich plasma (PRP) are not allowed within 3 months prior to a study assessment. The wash-out period of 3 months is based on clinical experience and evidence that the effects of PRP and steroid injections seem to wear off after 3 months [20].

### Outcome measures

Validated Swedish versions of all patient-reported outcome measures (PROM) are used. Grip strength, range of motion (ROM), static two-point discrimination (S2PD), and Mini Sollerman test are measured according to the Swedish standard for assessment of hand and upper limb measurements developed by the Swedish Healthcare Quality Registry for hand surgery (HAKIR). PROMs are collected at baseline, 3 and 6 months, and 1 year after intervention. Objective physical variables are assessed at baseline, at 3 and 6 months, and 1 year. S2PD and Mini Sollerman are tested at baseline and 3 and 6 months after intervention. Baseline assessments and measurements at 3 and 6 months and 1 year after intervention are performed by an experienced physiotherapist or occupational therapist.

### Primary outcome measure

The primary outcome measure is as follows: pain on load in the included finger (as measured by the pain numerical rating scale (NRS), item 1 in the HAKIR eight-item participant questionnaire (HQ8) score, see below) 1 year after the intervention.

### Secondary outcomes measures

#### Pain numerical rating scale (PNRS) at rest

PNRS is a numeric 11-point box scale. In this study, we use the NRS scale from HQ8 (see below) where each box represents numbers ranging from 0, 10, 20…up to 100 points. 0 corresponds to no pain and 100 the worst imaginable pain. The participants select a value that describes the perceived pain intensity in the included finger during the past week. Pain NRS is proven a valid and reliable pain scale in chronic musculoskeletal pain [21] and has a reported minimal clinically important difference (MCID) of 2 on a 0–10-point scale [22]. Finger pain on load is the primary outcome measure of this study, whereas finger pain at rest is a secondary outcome measure.

#### Patient-Rated Wrist and Hand Evaluation (PRWHE)

PRWHE [23] is a hand and wrist-specific PROM designed to evaluate pain and disability in daily living during the past week. The items are divided into a pain subscale (5 items) and a function subscale (10 items). Each item is coded from 0–10 points, and the total score ranges from 0 to 100. In calculation of the total score, pain and function scales are weighted equally. A higher PRWHE score indicates a worse disability. PRWHE is available in 21 languages and is recognized as a reliable and valid tool in patients with different wrist and hand injuries [24]. The suggested MCID of PRWHE is 14 [25].

#### The 8-item participant questionnaire (HQ8)

HQ8 is a PROM specifically developed for Swedish healthcare quality registry for hand surgery (HAKIR) [26]. It comprises 8 items evaluating pain on load, pain on motion without load, pain at rest, stiffness, weakness, numbness, cold sensitivity, and ability to perform daily activities during the past week in the hand/arm that has been operated on. Each item is graded on a numeric 11-point box scale (NRS-11) (0, 10…100). It is a single item questionnaire (a total score is not calculated). HQ8 has been shown to be reliable in both elective and traumatic hand conditions [26]. A MCID for HQ-8 has not been estimated.

#### EuroQol 5 dimensions 5 levels (EQ5D-5L)

EQ5D-5L [27] is one of the most common generic measurements of health-related quality of life and demonstrates excellent psychometric properties in different populations, conditions, and settings [28]. It comprises a visual analogue scale and a 5-item questionnaire regarding mobility, self-care, usual activities, pain/discomfort, and anxiety/depression. The response to each question is graded as the following: no, slight, moderate, severe, or extreme problems. A summary index value ranging from 0 to 1 is computed, where 0 represents death and 1 full health. Population reference data for Sweden is available [29]. The MCID of EQ5D-5L is sparsely studied in hand and wrist surgery but has been reported as 0.09 in carpal tunnel syndrome [30].

#### Grip strength and range of motion (ROM)

Grip strength is measured with a hydraulic hand dynamometer (BL5001, B&L Engineering®, Santa Ana, CA, USA). Three measurements at maximal grip are performed, and the mean in kilograms (kg) is calculated. ROM of the metacarpophalangeal (MCP), PIP, and distal inter phalangeal (DIP) joints are measured according to the “National manual for measuring motion and strength in the elbow, forearm and hand” (www.hakir.se) using a short-armed goniometer. Measurements are rounded up or down to the nearest 5° interval.

#### Mini Sollerman test

The Mini Sollerman test evaluates sensory function by measuring dexterity [31]. It is a shortened 3-task version of the original 20-task Sollerman test [32]. It comprises Sollerman tasks 4 (pick up coins from an open purse and put on the table), 8 (pick up screw-nuts and put them on the fitting bolts), and 12 (button four buttons with one hand). Each task is graded from 0 (the task could not be performed at all) to 4 (without difficulty, within 20 s and with the recommended hand grip) with a maximum total score of 12 points. To our knowledge, an MCID for Mini Sollerman has not been estimated.

#### Static two-point discrimination (S2PD)

S2PD measured by the Dellon-Mckinnon Disk-Criminator™ evaluates sensory function (discriminative touch) in the fingertips [33]. It measures the smallest distance in millimeters where a person is able sense the difference between two points of touch. S2PD is measured according to the “National assessment manual for assessment of hand function after nerve repair” (www.hakir.se).

#### Complications to treatment

All suspected complications to treatment will be recorded at the follow-up visits. Specifically, the presence of superficial or deep wound infections or loss of sensation will be recorded. S2PD and Mini Sollerman will be measured preoperatively, 3 and 6 months postoperatively to evaluate any differences in sensation before versus after treatment.

#### Need for analgesics

Consumption of paracetamol, NSAIDs, or opioids during follow-up will be recorded as a binary variable: Current pain medication, YES/NO. If yes: Type of medication and dose/day.

#### Failure

A hand surgeon performs clinical evaluations of all patients 3, 6, and 12 months after inclusion. The need for additional treatments is discussed at these appointments based on the patient’s symptoms and wishes. Failure of treatment is defined as the need for further surgery. The reason for additional surgery is noted. The date when a participant is enrolled on the waiting list for additional surgery is recorded, and the survival in months will be determined.

#### Sample size

SPSS version 29 was used for the sample size calculation. The reported MCID of NRS is 20 on a 100-point scale [22]. To our knowledge, the standard deviation (SD) of changes in pain scores in patients with PIP OA have not been previously reported. Hence, the SD is based on an estimation. SD will be calculated at the interim analysis, and the power calculation will be modified if necessary. To show a difference of 20 points in PNRS on load between intervention groups (estimated SD 30) after 12 months, 37 participants are required in each treatment arm. The power will be 80% (*p* < 0.05). To account for non-parametric outcome and loss to follow-up, we aim to include 90 participants in total, 45 in each treatment arm. Participants who withdraw from the trial before intervention will be replaced.

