**Methods:**

In this parallel-group, two-armed, randomized, controlled superiority trial (RCT), 90 participants are assigned to surgical PIP joint denervation or education and exercise. Pain on load 1 year after intervention is the primary outcome measure. Secondary outcome measures include pain at rest, Patient-Rated Wrist and Hand Evaluation (PRWHE), HQ8 score, EQ5D-5L, objective physical function, complications, two-point discrimination, Mini Sollerman, consumption of analgesics, and the need for further surgery. Assessments are performed at baseline, 3 and 6 months, and 1 year after intervention.

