### Data analyses

The data analyses plan was developed in cooperation with a medical statistician at the Department for Clinical Science and Education, Karolinska Institutet (KI SÖS). Analyses will be performed using an intention-to-treat approach. In addition, per-protocol analysis will be conducted for the primary outcome as sensitivity analysis per the actual treatment received. PROMs will be reported as median (interquartile range (IQR)) and continuous variables as mean (SD). For comparison of the differences between PIP denervation versus patient education and exercise, *T*-test will be used for continuous data with normal distribution, and chi-square tests will be used for categorical data. For non-normally distributed continuous data and ordinal data, the Wilcoxon signed rank tests will be used for within-patient comparisons and rank sum tests for between-patient comparisons. Normality will be assessed by QQ-plots. No subgroup or adjusted analyses are planned. Since there are only two treatment groups, any adjustment for multiple testing is not planned for the primary outcome. Significances of secondary outcomes will be adjusted using the Holm-Bonferroni method to control for multiple significance. Missing data will not be imputed.

The level of significance is set at *p* < 0.05. Demographic data and PROMs from dropouts will be described and compared to the participants that completed the trial. Interim analyses will be performed after 20 and 40 included participants. Data will be analyzed by R or SPSS.

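### The plan does not fix whether the assumed SD of 30, the interim SD and the tested pain variable are the same quantity, so the planned resizing could use an SD that does not match the test

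*Protocol article*

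**What the plan says.** All references are to the protocol article.

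- **Primary outcome.** The Abstract (Methods) states: "Pain on load 1 year after intervention is the primary outcome measure". The section Primary outcome measure identifies the variable as "item 1 in the HAKIR eight-item participant questionnaire (HQ8) score, see below) 1 year after the intervention". Neither place describes it as a change from baseline.
- **Origin of the SD.** The Sample size section says that "the standard deviation (SD) of changes in pain scores in patients with PIP OA have not been previously reported" and continues: "Hence, the SD is based on an estimation".
- **Re-estimation.** The next sentence reads: "SD will be calculated at the interim analysis, and the power calculation will be modified if necessary". It does not say which SD.
- **Calculation.** The target is a "difference of 20 points in PNRS on load between intervention groups (estimated SD 30) after 12 months", which needs 37 per arm for 80% power. This is raised to 45 per arm for loss to follow-up and a non-parametric outcome.
- **Analysis.** The Data analyses section offers a t-test or a rank-sum test between groups and adds: "No subgroup or adjusted analyses are planned". It does not say whether the test is applied to 12-month scores or to changes. It sets the interim analyses at 20 and 40 included participants.

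**The concern.** The power of a comparison depends on the SD of the variable that is tested. An unadjusted comparison of 12-month scores depends on the SD of those scores. A comparison of changes depends on the SD of changes. The two generally differ, by an amount set by the correlation between baseline and 12-month pain and by the SDs at the two times.

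The only SD that the Sample size section describes in words is that of changes. The sentences on the estimate and on the interim follow directly from it. The outcome definition and the calculation sentence point instead to the 12-month score. A guessed SD would do little harm alone, since any planning value may be wrong. Here the plan also intends to act on an observed SD. If the interim computes one quantity and the final test uses another, the trial could be shortened to a size that cannot deliver the intended power, or extended without need.

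**Working it through.** **Inputs.** From the Sample size section: difference 20, SD 30, power 80%, significance level 0.05, 37 per arm. From Randomization, allocation, and blinding: 1:1 allocation. Assumptions of this review: a two-sided test (a one-sided test would give 28 per arm, so 37 implies two-sided), equal SDs at baseline and 12 months, and a baseline-to-12-month correlation r, which the document does not give.

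**Step 1: reproduce the plan's figure.** By the normal approximation, n per arm = 2 × (1.960 + 0.842)² × (30/20)² = 15.70 × 2.25 = 35.3, so 36. With the exact (noncentral t) calculation, 36 per arm gives 79.7% power and 37 gives 80.8%. The plan's 37 is confirmed. The arithmetic is the same whichever SD the 30 stands for.

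**Step 2: relate the two SDs.** In general, SD_change² = SD_base² + SD_12² − 2 r SD_base SD_12. With equal SDs this becomes SD_change = SD_12 × √(2(1 − r)), and the two SDs coincide at r = 0.5. Without equal SDs they coincide at r = SD_base / (2 × SD_12). For example, SDs of 20 at baseline and 30 at 12 months put that point at r = 20/60 = 0.33.

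**Step 3: the 12-month SD is 30, the interim resizes on the change SD, and 12-month scores are tested.** Sizes and powers are for the t-test.

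| r | SD of change | n per arm after resizing | true power of the 12-month comparison |
|---|---|---|---|
| 0.3 | 30 × √1.4 = 35.5 | 51 | 92% |
| 0.5 | 30 × √1.0 = 30.0 | 37 | 81% |
| 0.6 | 30 × √0.8 = 26.8 | 30 | 72% |
| 0.7 | 30 × √0.6 = 23.2 | 23 | 60% |

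At r = 0.3 the trial would be 51 − 37 = 14 per arm larger than needed. At r = 0.7 it would be 37 − 23 = 14 per arm too small.

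**Step 4: the 30 is itself the SD of change, and 12-month scores are tested.** The 12-month SD is then 30 / √(2(1 − r)): 25.4 at r = 0.3, 30.0 at 0.5 and 38.7 at 0.7. The required sizes are 27, 37 and 60 per arm. With 37 per arm, power is 92%, 81% and 59%. With all 45 per arm evaluable, it is 96%, 88% and 68%.

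**Step 5: what the interims could see.** Trial status gives recruitment from September 2023 to 2027. If 90 participants accrue evenly over about 3.3 to 4.3 years, the 20th is included after 20/90 of that time, about 0.7 to 1.0 years, before anyone has 12-month data. The 40th is included after about 1.5 to 1.9 years, when roughly 13 to 19 participants have passed 12 months. An interim run at the first stated trigger could therefore not produce a 12-month SD or a 12-month change SD.

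**Step 6: the adjusted analysis.** Adjusting for baseline reduces the SD to about 30 × √(1 − r²): 28.6, 26.0 and 21.4 at r = 0.3, 0.5 and 0.7. The required sizes are 34, 28 and 20 per arm. A planning SD of 30 for the 12-month score is thus conservative for the adjusted analysis.

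**The case against.** The strongest reply is that no error has been shown. The reference to changes appears only in the sentence on what the literature lacks. The calculation sentence ties 30 to a between-group difference after 12 months, in line with the outcome definition, and the re-estimation sentence says only SD. Ruling out adjusted analyses does not settle the tested variable either, because a t-test or rank-sum test on changes is also unadjusted. If scores are used throughout, or changes throughout, nothing is wrong. Harm needs a mixture of the two that no passage states, and the plan gives no rule for cutting the sample size. The sizes above also depend on equal SDs, on an unknown r and on a t-test, whereas the Data analyses section sends ordinal and non-normal data to rank tests. Finally, the details of an interim SD are commonly left to the analysis plan.

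Most of this stands, and it limits the point. A reader might infer that the sample size was built on the SD of changes, or that 37 is wrong. The documents support neither. What remains is that the protocol itself names one quantity as the reason for its SD, defines the outcome as another, and commits to revising the calculation on an SD it does not identify. That is an inconsistency in the stated text, not a detail left for later.

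**Conclusion.** The point holds as an ambiguity with possible consequences, not as a demonstrated error in the sample size. The document does not fix whether the 30, the interim SD and the tested variable are one quantity. The 37 per arm is correct for its inputs.

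If the change SD drove the resizing and unadjusted 12-month scores were tested, the outcome would range from 23 per arm with 60% power (r = 0.7) to 51 per arm (r = 0.3), with no error at r = 0.5. These figures assume SDs of 30 at both times, a t-test, and an interim that acts fully on the observed SD. The range of r is an assumption. The matter should be settled before any interim SD is used.

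**What to change.** 1. For the primary outcome, replace the statement that no adjusted analyses are planned with a comparison of the 12-month pain-on-load score adjusted for baseline pain and for sex, the stratification factor.
2. State that the SD of 30 refers to the 12-month score.
3. Base any re-estimation on the pooled SD of that same score, or on the residual SD of the adjusted model, in participants who have reached 12 months, without comparing the arms. Tie its timing to the number with 12-month data, not to the number included.
4. Optionally, state that re-estimation will not take the trial below 37 analysed per arm.

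The cost is a change of wording and a slightly different interim calculation. No new data are needed, since baseline pain and sex are already collected, and the required size does not rise. If the sponsor prefers to keep the unadjusted test, the minimum is one sentence saying whether 30 is the SD of the 12-month score or of change, with that same quantity used in the test and at the interim.

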### Data analyses

The data analyses plan was developed in cooperation with a medical statistician at the Department for Clinical Science and Education, Karolinska Institutet (KI SÖS). Analyses will be performed using an intention-to-treat approach. In addition, per-protocol analysis will be conducted for the primary outcome as sensitivity analysis per the actual treatment received. PROMs will be reported as median (interquartile range (IQR)) and continuous variables as mean (SD). For comparison of the differences between PIP denervation versus patient education and exercise, *T*-test will be used for continuous data with normal distribution, and chi-square tests will be used for categorical data. For non-normally distributed continuous data and ordinal data, the Wilcoxon signed rank tests will be used for within-patient comparisons and rank sum tests for between-patient comparisons. Normality will be assessed by QQ-plots. No subgroup or adjusted analyses are planned. Since there are only two treatment groups, any adjustment for multiple testing is not planned for the primary outcome. Significances of secondary outcomes will be adjusted using the Holm-Bonferroni method to control for multiple significance. Missing data will not be imputed.

The level of significance is set at *p* < 0.05. Demographic data and PROMs from dropouts will be described and compared to the participants that completed the trial. Interim analyses will be performed after 20 and 40 included participants. Data will be analyzed by R or SPSS.

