### Randomization, allocation, and blinding

All hand surgeons (> 20) working at the Department of Hand Surgery at Södersjukhuset may enroll participants. The hand surgeon in charge of the participant’s treatment collects informed consent. On the day of enrollment, a dedicated research nurse randomly assigns participants (1:1) to one of the treatment arms using sealed, unnumbered envelopes. A block randomization scheme with a fixed block size of 10 is used. The envelopes containing the allocation slips are prepared and mixed by the primary investigator. Participants are stratified according to sex, since idiopathic OA may be more common in women and men are more likely to have posttraumatic OA than women [18]. Blinding of participants and assessors is considered unfeasible due to a scar on an operated finger. Data analysts are blinded to treatment allocation (anonymized data sheets, with treatment arms coded as A or B by an external part before analyses). Participants in the non-operative treatment group are offered denervation surgery after the study’s primary endpoint (12 months). Cross-over during the study period is not allowed.

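### The primary comparison is planned without adjustment for baseline pain on load or sex, which gives up precision already paid for and fits poorly with a sample size built on a 20-point mean difference

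*Protocol article*

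**What the plan says.** The primary outcome is pain on load in the included finger one year after the intervention, taken from item 1 of the HQ8 (Primary outcome measure). It is scored on an 11-box scale where "each box represents numbers ranging from 0, 10, 20…up to 100 points" (section on pain NRS at rest).

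Two pieces of baseline information are built into the design. Under Outcome measures, "PROMs are collected at baseline, 3 and 6 months, and 1 year after intervention", so pain on load is available before treatment. Under Randomization, allocation, and blinding, "Participants are stratified according to sex".

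The Data analyses section uses neither: "No subgroup or adjusted analyses are planned". It assigns a t-test to normally distributed continuous data and rank-sum tests to non-normal or ordinal data, and adds that "Normality will be assessed by QQ-plots". PROMs are to be summarised by median and IQR, and continuous variables by mean and SD. The article does not say whether the pain NRS counts as ordinal or continuous.

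The Sample size section is framed in points: "To show a difference of 20 points in PNRS on load between intervention groups (estimated SD 30) after 12 months, 37 participants are required". That number is per arm, and it is raised to 45 to cover a non-parametric outcome and loss to follow-up.

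**The concern.** Baseline pain on load is likely to predict pain on load a year later. Leaving it out keeps variance in the comparison that could be removed at no cost. With about 40 per arm, the arms can also differ in baseline pain by chance, and an unadjusted analysis carries part of that difference into the estimate. Sex was thought important enough to stratify on, but is then dropped from the analysis.

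The second issue is what the result can be read against. The trial is sized for a mean difference of 20 points, the MCID that the article cites. A rank-sum p-value with two medians, on a scale that moves in steps of 10, does not directly estimate a mean difference. The Discussion says that denervation should not be used unless it does better than non-surgical treatment. That judgement calls for an effect in points with an interval.

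**Working it through.** **Inputs from the article.** Difference 20, SD 30, 80% power, significance level 0.05 and 45 recruited per arm (Sample size, Data analyses); 1:1 allocation (Randomization).

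**Assumptions not in the article.**
- The test is two-sided.
- Loss to follow-up is 15%: 45 × 0.85 = 38.25, so 38 analysed per arm.
- The correlation r between baseline and 12-month pain on load is 0.3 to 0.5.
- 30 is the SD of the 12-month score.
- The rank-sum test has efficiency 0.955 relative to the t-test.

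**Step 1: the plan's own figure.** A two-sided two-sample t-test with noncentrality 20 / (30 × √(2/n)) has power 79.7% at n = 36 and 80.8% at n = 37. The stated 37 per arm is therefore reproduced. It is an unadjusted t-test on means.

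**Step 2: power as planned, 38 per arm.**
- t-test: 81.8%.
- Rank-sum: effective n = 38 × 0.955 = 36.3, giving about 80.0%.

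**Step 3: power with baseline adjustment, 38 per arm.** Residual SD = 30 × √(1 − r²), with two degrees of freedom fewer for baseline pain and sex. No gain is credited to sex.

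| r | Residual SD | Variance removed (r²) | Power |
|---|---|---|---|
| 0.3 | 28.6 | 9% | 85.2% |
| 0.4 | 27.5 | 16% | 87.9% |
| 0.5 | 26.0 | 25% | 91.2% |

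**Step 4: chance imbalance.** If the baseline SD is also 30, the standard error of the baseline difference between arms is 30 × √(2/38) = 6.9 points, about a third of the 20-point target. With equal SDs the regression slope equals r. At r = 0.5, an imbalance of one standard error therefore moves the unadjusted estimate by 0.5 × 6.9 = 3.4 points.

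**Step 5: validity and the bounded scale.** Scores were simulated on a rounded 0 to 100 scale, with 37 per arm, r = 0.5, an assumed sex effect of 15 points and 4,000 runs.
- With no treatment effect, rejection rates were 4.0% (t-test), 3.8% (rank-sum) and 4.9% (adjusted model). The unadjusted tests are slightly conservative, not inflated.
- With a 20-point shift before bounding, power was 77%, 76% and 88%. At r = 0.3 it was 77%, 76% and 82%. The gain survives the coarse scale.

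**The case against.** The strongest reply is that nothing here is invalid. The unadjusted test holds its error rate, the 37 per arm is right for it, and on the assumptions above it reaches its stated 80% power. It was chosen in advance with a medical statistician. All of that stands, and it limits the point to precision and interpretability. The size of the gain also rests on a correlation that the article does not give, and it is modest at 0.3.

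A separate analysis plan could name an effect estimate for the rank-sum route, such as a Hodges-Lehmann shift with an interval in points. The absence of one from an article is therefore not a fault in itself. That reply does not reach the adjustment point, because the article rules adjustment out in so many words.

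A reader might draw two stronger conclusions, and the article supports neither.

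- **That the primary test is picked by QQ plot once the outcome has been seen.** The Data analyses section separates PROMs from continuous variables and sends ordinal data to the rank-sum test with no normality condition. The Sample size section already allows for a non-parametric outcome. For an 11-box PROM item the natural reading is a rank-sum test fixed in advance. What remains is that the class of the NRS is not spelled out.
- **That the trial would have only 68% power on change scores.** The Sample size section does remark that "the standard deviation (SD) of changes in pain scores in patients with PIP OA have not been previously reported", but the primary outcome is defined as pain at one year and no change-score test is named. The 68% arises only at r = 0.3 with 30 taken as the SD of the 12-month score (change SD 30 × √(2 × 0.7) = 35.5). At r = 0.5 the change SD is 30 and power is 81.8%. If 30 is itself the SD of change, a change-score test also has 81.8%.

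**Conclusion.** The point holds as a recommended improvement, not as an error of inference. Ruling out adjustment costs about 3 to 9 percentage points of power against the t-test (81.8% against 85.2% to 91.2%) and about 5 to 11 against the rank-sum test (80.0%). It also leaves chance imbalance in baseline pain uncorrected. These figures assume 38 analysed per arm, an SD of 30 for the 12-month score, and a correlation of 0.3 to 0.5.

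The mismatch between a rank-sum test with medians and a sample size set on a 20-point mean difference does not depend on those assumptions. It follows from the natural reading of the analysis section. The documents show no bias, no inflated type I error and no shortfall from the stated power.

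**What to change.** For the primary outcome, replace the sentence that excludes adjusted analyses with wording such as: *The primary analysis is a linear model of 12-month pain on load on treatment arm, baseline pain on load and sex. It reports the adjusted mean difference with its 95% confidence interval, using robust standard errors, read against 20 points. A rank-sum test is a sensitivity analysis.* The statement that no subgroup analyses are planned can stay.

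Use the same baseline-adjusted form for the secondary outcomes that are analysed as continuous, such as grip strength and range of motion.

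The change needs no new data, visits or participants. It is a protocol amendment, and the Trial status section says that important modifications require permission from the ethical review board. Recruitment is expected to run until 2027, so there is time to make it before the final analysis. It should be dated and made without sight of any comparison of pain between arms. The model treats an 11-box scale as numeric; the sample size calculation already does so, and the robust standard errors and the rank-sum sensitivity analysis cover most of that concern.
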